## 12. Data analysis

A data safety officer will monitor the study. The primary and secondary outcomes will be analysed using the intention-to-treat approach. Differences in baseline characteristics and clinical outcomes between the two groups will be evaluated using two-sample t-tests for continuous variables and chi-square tests for categorical variables.

For the primary outcome, the cumulative incidence of T2DM will be compared between the two groups using a log-rank test with random effects for intercept to account for pre-post correlations within participants. The intervention effect will be assessed at each time point. For secondary outcomes, which will be continuous variables, repeated-measure linear mixed models will be used to assess differences between groups over time.

The incidence rate of diabetes will be calculated by dividing the number of new diabetes cases by the total person-time of follow-up, expressed per 1,000 person-years. This method will account for participants with differing lengths of follow-up, including those who drop out or are lost to follow-up. Incidence rates will be

reported as events per 1,000 person-years, along with 95% confidence intervals (CIs), to provide a measure of precision and enable comparisons between groups.

The cumulative incidence of T2DM over the 12-month follow-up period will be estimated using Kaplan-Meier survival analysis. Differences between the survival curves will be tested using the log-rank test to determine statistical significance. To quantify the intervention effect, hazard ratios (HRs) with 95% CIs will be calculated using a Cox proportional hazards regression model, which will adjust for the time to diabetes development. Participants who do not develop T2DM or are lost to follow-up will be censored at the time of their last follow-up, ensuring accurate risk estimation.

For intervention measures, chi-square tests will be used to compare event rates between the intervention and control groups. Absolute risk reduction (ARR) and relative risk reduction (RRR) will be calculated, with risk ratios used to quantify the relative difference in event rates between the two groups. Confidence intervals for ARR and RRR will be computed to estimate the precision of the findings. The number needed to treat (NNT) to prevent one case of T2DM will be determined to evaluate the practical impact of the intervention.

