Changes in biophysical, clinical, and laboratory parameters will be analyzed using a difference-in-differences approach, comparing changes within and between the intervention and control groups over time. This method will account for baseline differences and provide a robust estimate of the intervention effect. The difference-in-differences approach will be chosen because it isolates the intervention effect by controlling for time-invariant differences between groups and common trends over time. All analyses will be adjusted for clustering at the mosque level using mixed-effects models to account for intraclass correlation. Statistical significance will be set at  $p < 0.05$ , and all analyses will be performed using STATA version 17.0 (StataCorp, College Station, TX, USA) and the statistical package SPSS (PASW Statistics 20).

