### 3. Trial Design and Randomization

A cluster-randomized parallel-group design was used with 8 mosques as units of randomization. Mosques were randomized 1:1 to intervention or control groups using a computer-generated block randomization schedule (block size = 2), stratified by district. The allocation sequence was prepared by an independent statistician. Field staff enrolled participants and assigned them post-randomization.

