**Analysis:**

- Kaplan-Meier survival curves estimated cumulative incidence.
- Group comparisons were assessed via log-rank test.
- Cox proportional hazards model with shared frailty for mosque-level clustering was used.
- HRs with 95% CIs were reported.
- The assumption of proportional hazards was tested using Schoenfeld residuals.

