**Analysis:**

- Linear mixed-effects models were used for continuous outcomes with mosque-level random intercepts.
- Generalized estimating equations (GEE) were used for binary outcomes with robust SEs and exchangeable correlation structure.
- All models adjusted for baseline values.
- Difference-in-differences approach was used to estimate net intervention effect.

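### The primary outcome has no named deciding test: SAP 7.2 lists a log-rank test with no mosque term beside a shared-frailty Cox model with no small-sample correction for eight clusters

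*Combined protocol and SAP*

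**What the plan says.** **Design.** SAP section 3: "A cluster-randomized parallel-group design was used with 8 mosques as units of randomization". It adds: "Mosques were randomized 1:1 to intervention or control groups using a computer-generated block randomization schedule (block size = 2), stratified by district".

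**Primary outcome, SAP 7.2.** Cumulative incidence is estimated by Kaplan-Meier. Then "Group comparisons were assessed via log-rank test", followed by "Cox proportional hazards model with shared frailty for mosque-level clustering was used", with hazard ratios and 95% confidence intervals. Neither line is marked as the deciding one.

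**Primary outcome, protocol section 12.** One sentence says that "the cumulative incidence of T2DM will be compared between the two groups using a log-rank test with random effects for intercept". The stated purpose of that random effect is the before-and-after correlation within a participant, not the mosque. The same section later lists a plain log-rank test and a plain Cox model. It also says that "chi-square tests will be used to compare event rates between the intervention and control groups", and follows this with absolute and relative risk reductions and their intervals, and a number needed to treat.

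**General rule, end of protocol section 12.** "All analyses will be adjusted for clustering at the mosque level using mixed-effects models to account for intraclass correlation".

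**Secondary binary outcomes, SAP 7.3.** "Generalized estimating equations (GEE) were used for binary outcomes with robust SEs and exchangeable correlation structure".

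Neither document mentions a t reference, a degrees-of-freedom correction, a permutation test or a cluster-level analysis.

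**The concern.** When whole mosques are randomized, the information about the treatment effect is limited by the number of mosques. A test that treats about 800 people as independent understates the variance and rejects a true null hypothesis too often.

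The log-rank test in SAP 7.2 does this. The protocol does not repair it. A log-rank or chi-square test has no place for a random effect, so the general promise of mixed-effects adjustment cannot apply to either. The one random effect that the protocol attaches to a log-rank test concerns the wrong correlation, because people with diabetes at baseline are excluded.

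The frailty Cox model does address mosques. With four per arm, however, a variance estimated from so few clusters and referred to a normal distribution is also too optimistic. Two tests with very different error rates and no rule between them leave the trial's main claim without a known type I error.

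**Working it through.** **Inputs**
- Clusters: 8 mosques, 4 per arm (SAP section 3).
- Analysed sample: 799, so 799/8 = 99.875 per mosque; range 92 to 110 (SAP section 4).
- ICC: 0.041 for planning and 0.039 observed (SAP section 4); 0.05 (protocol 10.6). An ICC of 0.02 is my assumption, to show a lower value.
- Two-sided alpha of 0.05 (SAP section 9).

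**Step 1. Reproduce the plan's design effect.** DE = 1 + (m − 1) × ICC. With the protocol's figures, 1 + (103 − 1) × 0.05 = 6.1, as stated in protocol 10.6. The formula therefore matches the plan's own use.

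**Step 2. Type I error of a test without a mosque term.** The test statistic has true variance DE where 1 is assumed, so the error is 2 × [1 − Φ(1.96/√DE)].

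| ICC | DE (m = 99.875) | 1.96/√DE | Type I error |
|---|---|---|---|
| 0.02 (assumed) | 2.98 | 1.136 | 25.6% |
| 0.039 | 4.86 | 0.889 | 37.4% |
| 0.041 | 5.05 | 0.872 | 38.3% |
| 0.05 | 5.94 | 0.804 | 42.1% |

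With m = 103 at ICC 0.05 (DE 6.1), the result is 42.7%. This step needs no assumption about null risk or event timing.

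**Step 3. Simulation under the null.** There were 4,000 trials per setting, with 8 mosques of 100 and beta-binomial mosque risks. Assumed: 12-month risk of 8.5% or 12% in both arms, events found only at months 4 and 12, one third of the hazard falling by month 4, and district stratification ignored. Rejection rates at nominal 5%, as the range over the two risks:

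| ICC | Log-rank | Frailty Cox, Wald z | GEE, robust z | Mosque-level t, 6 df |
|---|---|---|---|---|
| 0.02 | 25.2–25.7% | 12.3–12.4% | 14.2–14.7% | 4.8–5.1% |
| 0.039 | 36.4–37.5% | 13.0–13.1% | 14.3–14.9% | 4.4–4.7% |
| 0.041 | 38.5–39.6% | 13.2–13.4% | 14.7–15.0% | 4.4–4.7% |
| 0.05 | 41.1–43.9% | 13.2–15.2% | 15.6–16.5% | 4.4–5.7% |

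A separate run of 2,000 trials at 12% risk and ICC 0.039 gave 37.5%, 13.9%, 15.0% and 5.0%. Referring the frailty Wald statistic to t on 6 df lowers its rate to about 7% to 9% at ICC 0.039 to 0.05.

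**Step 4. Analytic check of the uncorrected robust SE.** With four clusters per arm, the sandwich variance is too small on average by the factor 3/4. So P(|t₆| > 1.96 × √(3/4)) = P(|t₆| > 1.697) = 14.1%, in line with the GEE column.

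**Step 5. Interval width.** For an interval computed without clustering, the needed widening at ICC 0.039 is √4.86 × 2.447/1.96 = 2.204 × 1.248 = 2.75. For the frailty hazard ratio, where clustering is already modelled, the t reference alone gives 2.447/1.96 = 1.25.

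**Step 6. Power of the mosque-level test.** For 12% versus 5% with 400 per arm and DE = 1 + 99 × 0.039 = 4.86, SE = √[4.86 × (0.12 × 0.88 + 0.05 × 0.95)/400] = 0.0431. The noncentrality is 0.07/0.0431 = 1.62. Against the critical value 2.447 on 6 df, power is 27.8% (26.9% at ICC 0.041, 23.6% at 0.05).

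**The case against.** The best defence is that the plan does adjust for mosques. The only effect estimate in SAP 7.2 is a hazard ratio from a mosque-frailty model, and the protocol promises mosque-level adjustment throughout. Four stronger readings that a reader might infer are not supported.

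- *The log-rank test is the primary test.* SAP 7.2 does not say so. The defect is an unadjusted test together with an unspecified deciding test.
- *Robust standard errors underpin the primary result.* They are specified only for secondary binary outcomes, whose results SAP section 6 calls exploratory.
- *The trial's error rate is a single range from about 14% to 38%.* No one test has that range. It depends on which test decides.
- *Every interval should be 2.75 times as wide.* That factor applies to intervals that ignore clustering. The frailty hazard ratio already models it.

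It is also fair to say that the chi-square test and the risk-reduction measures come from the protocol. The SAP uses chi-square only for baseline description. The normal Wald reference for the frailty model is my assumption, since SAP 7.2 names none. An ICC from eight mosques is imprecise.

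Stratification by district could lower the error rates if districts differ. Its help is limited: eight mosques in five districts cannot all form within-district pairs, since at least two districts must hold an odd number, and no listed primary analysis includes district.

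Nothing in the documents shows that a test was chosen for its result.

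What remains is that the log-rank test has no mosque term, the general promise cannot reach it, and nothing is adapted to eight clusters.

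**Conclusion.** The concern holds in this form: neither route that SAP 7.2 offers to a primary p-value has a demonstrated 5% error rate, and the plan does not choose between them.

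If the log-rank test decides, the type I error is about 37% to 38% at the SAP's ICCs, about 42% at the protocol's 0.05, and about 25% at an assumed 0.02. If the frailty Cox model decides on a normal Wald test, it is about 13% to 14% at the SAP's ICCs, subject to the simulation assumptions in step 3. Unclustered intervals for the risk reductions and number needed to treat would need to be about 2.75 times as wide. The hazard-ratio interval is too narrow by much less, about 1.25-fold from the t reference alone. For secondary binary outcomes, uncorrected robust standard errors give about 14% to 15%.

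The SAP's stated post-hoc power of 82% is a separate matter, and this conclusion does not depend on it.

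**What to change.** 1. Name one primary analysis that accounts for mosque clustering with a small-sample method. One example is a mosque-level comparison of 12-month incidence, four against four, on 6 df. Other small-sample methods are possible if their error rate is shown to be near 5% with eight clusters. The t₆ reference alone did not quite achieve this for the frailty model (about 7% to 9%).
2. Report no unadjusted log-rank or chi-square p-value. Keep the Kaplan-Meier curves as description.
3. Derive the intervals for absolute and relative risk reduction and number needed to treat from the same clustered analysis.
4. Apply a small-sample correction to the GEE for secondary binary outcomes.
5. State how district stratification is handled in the chosen analysis.

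**Cost.** SAP wording and a re-run on existing data; no new data collection. Intervals become wider, and the mosque-level test has power of only about 28% for 12% versus 5%. That is a limit of a design with eight clusters and should be disclosed. The SAP declares that it was written after data collection ended, and it already reports an observed ICC. The change must therefore be labelled as made after data collection, with the listed analyses shown alongside as sensitivity results, without unadjusted p-values.

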### 7.3 Secondary Outcomes

**Outcomes:** Weight, BMI, FPG, 2hPG, HbA1c, HDL, blood pressure, physical activity, diabetes knowledge, EQ-5D-5L score.

**Analysis:**

- Linear mixed-effects models were used for continuous outcomes with mosque-level random intercepts.
- Generalized estimating equations (GEE) were used for binary outcomes with robust SEs and exchangeable correlation structure.
- All models adjusted for baseline values.
- Difference-in-differences approach was used to estimate net intervention effect.

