## 10. Research methodology

### 10.1 Study design and participants

This cluster-randomized controlled trial (RCT) will be conducted across eight mosques in rural villages of five districts in Bangladesh: Manikganj, Narshingdi, Munshigonj, Dhaka, and Tangail. The study will target rural areas to address the unique challenges faced by these communities. Participants will be randomly allocated to either the intervention or control group at the cluster level (mosques). Eight mosques will be selected using a simple random procedure, with four assigned to the intervention group and four to the control group. Mosques will be randomly assigned as intervention or control sites using block randomization to ensure geographic diversity and balance across groups. Randomization lists will be generated centrally and concealed from field teams to minimize bias. Intervention centers will be in Shibaloy, Monohardi, Raipura, and Dhanbari, while control centers will be in Singair, Keraniganj, Sreenagar, and Sakhipur. All mosques are recognized by the Islamic Foundation of the Ministry of Religious Affairs and have an education center for learning the Holy Quran.

Participants will be recruited using the most recent voter list and age distribution data for Bangladesh. Each site will have an estimated population of 2,500 to 3,000 individuals, from which 1,500 individuals aged 25 to 65 years will be invited to participate. According to Bangladesh's age distribution, 45–47% of the population falls within this age group [30, 31]. The target recruitment goal is to enroll up to 108 participants from each mosque.

Recruitment will initiate at each mosque 4 weeks before the introduction of the intervention. The Imams will discuss and convey the message of a healthy lifestyle including diet and exercise during the Friday sermon and use a standardized script to encourage congregational participation in practice. They will distribute investigator-developed flyers to congregational participants to promote the study objectives. They will also discuss the importance of female participation as part of the intervention. Members of the research team will also attend Friday sermons to assist with recruitment and provide information regarding the study.

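### SAP 7.3 names a mosque random intercept, baseline adjustment and difference-in-differences for continuous secondary outcomes, but these do not form one coherent model, and on either reading the intervals can be wrong

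*Combined protocol and SAP*

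**What the plan says.** SAP 7.3 gives the analysis of secondary outcomes as separate bullets, three of which bear on the continuous outcomes:

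- "Linear mixed-effects models were used for continuous outcomes with mosque-level random intercepts". No other random effect is named.
- "All models adjusted for baseline values". The form of the adjustment is not stated.
- "Difference-in-differences approach was used to estimate net intervention effect".

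There is no model equation. The SAP does not say whether the baseline value is an outcome row, a covariate for later values, or both. It names no arm-by-time, participant or mosque-by-time term and no small-sample degrees of freedom.

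Protocol section 12 says that for continuous secondary outcomes "repeated-measure linear mixed models will be used to assess differences between groups over time". It describes difference-in-differences as "comparing changes within and between the intervention and control groups over time" and adds: "All analyses will be adjusted for clustering at the mosque level using mixed-effects models to account for intraclass correlation". Protocol section 11 sets measurements at baseline, 4 and 12 months. Allocation is by mosque, eight in all, "with four assigned to the intervention group and four to the control group" (protocol 10.1).

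**The concern.** In a stacked model with baseline as one of the outcome rows, the difference-in-differences effect is the arm-by-time term. A mosque effect that is constant over time adds equally to a mosque's baseline and follow-up values, so it drops out of every change. What remains, and what matters when arm is assigned by mosque, is how far the average change differs between mosques. That component is not in the model SAP 7.3 names, so the protocol's undertaking to adjust all analyses for mosque clustering would not be met for the effect of interest. Such variation is plausible because each mosque's own imam and female assistant deliver the sermons and walks (protocol 10.9).

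The baseline adjustment makes this worse. In a stacked fit the covariate explains part of the outcome rows, including the baseline row itself. It lowers the residual variance without adding information on change.

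At stake are the intervals and p-values for the continuous outcomes in SAP 7.3, such as weight, BMI, glucose, HbA1c, HDL and blood pressure. The SAP's own hypothesis (SAP 2) includes greater cardiometabolic improvement, and SAP 9 sets two-sided 0.05 as the criterion.

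**Working it through.** The documents give no figure for this model, so there is none to reproduce. The check uses algebra and simulation under no effect.

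**Inputs from the documents.** 8 mosques, 4 per arm; 396 and 403 participants, cluster sizes 92 to 110, observed ICC 0.039 (SAP 4; borrowed here for the secondary outcomes); three visits.

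**Assumptions not in the documents.** Total variance 1; within-person correlation ρ of 0.6 or 0.8; share of mosque variance stable over time, CAC, of 1.0, 0.8 or 0.5. Complete data. 1,500 simulated trials per case unless stated.

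**Step 1. True variance of the estimated difference in change (baseline to 12 months).**

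Variance = ICC × (1 − CAC) + 2 × (1 − ICC) × (1 − ρ) × (sum of 1/m over mosques)/16, where m is mosque size.

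With m close to 100 the last factor is about 0.00501. For ρ = 0.6 the participant part is 2 × 0.961 × 0.4 × 0.00501 = 0.00385.

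- CAC 1.0: √0.00385 = 0.062
- CAC 0.8: √(0.0078 + 0.00385) = 0.108
- CAC 0.5: √(0.0195 + 0.00385) = 0.153

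The simulated SDs were 0.063, 0.110 and 0.150.

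**Step 2. Standard error from the stacked model, mosque intercept only, no baseline covariate.**

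SE² = 2 × residual variance × (1/396 + 1/403). With residual variance 0.961, SE = √(2 × 0.961 × 0.005007) = 0.098. The simulated SE was 0.098 at all three CAC values. Raising a fully stable ICC to 0.20 does not increase it: √(2 × 0.80 × 0.005007) = 0.0895 (simulated 0.089).

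**Step 3. Add baseline as a covariate.** With complete data the estimate is unchanged (largest difference about 2 × 10⁻¹⁵). The standard error is not. Ignoring the small mosque term, the pooled slope on baseline over three visits is b = (1 + 2ρ)/3, and the residual variance falls by the factor 1 − b².

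- ρ = 0.6: b = 0.733, √(1 − 0.538) = 0.68 (simulated ratio 0.68, a 32% reduction)
- ρ = 0.8: b = 0.867, √(1 − 0.751) = 0.50 (simulated ratio 0.50, a 50% reduction)

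**Step 4. Rejection rate of a nominal 5% test, stacked model with baseline covariate, normal reference.**

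| CAC | ρ | Model SE | True SD | SE/SD | Rejects |
|---|---|---|---|---|---|
| 1.0 | 0.6 | 0.0667 | 0.0627 | 1.06 | 3.5% |
| 0.8 | 0.6 | 0.0669 | 0.1100 | 0.61 | 23.5% |
| 0.5 | 0.6 | 0.0674 | 0.1503 | 0.45 | 38.9% |
| 0.8 | 0.8 | 0.0493 | 0.0989 | 0.50 | 32.0% |

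The row at CAC 0.8, ρ 0.6 can be checked by hand: 1.96 × 0.61 = 1.19, and a standard normal exceeds that in absolute value about 23% of the time. Without the covariate the same case rejects 7.5%. A separate, smaller simulation at ρ = 0.6 (150 runs per case, some fits with convergence warnings) gave 2%, 19% and 45% as mosque-by-time variance rose. The range of 19% to 45% covers both sets of runs.

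The size is sensitive to the inputs. With 400 runs per case and CAC 0.8, the rate was 16.5% at ICC 0.039 and ρ 0.4, and 9.5% at ICC 0.01 and ρ 0.6.

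**Step 5. The other reading: 12-month value on arm and baseline, with a mosque intercept.** Here mosque variance does enter. At CAC 1.0 and ρ 0.6 the model SE rises from 0.077 (ICC 0.039) to 0.127 (ICC 0.20), against true SDs of 0.080 and 0.137. At ICC 0.039 the test rejects 8.5% to 9.9% with a normal reference and 4.0% to 5.4% on 6 degrees of freedom. With the smaller simulation included, the normal-reference range is about 8% to 11%. This is what few clusters would lead one to expect: a t variable on 6 df exceeds 1.96 in absolute value 9.8% of the time.

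**Step 6. Mosque mean changes compared 4 versus 4 on t with 6 df.** Rejects 4.5% to 5.3% at ICC 0.039.

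**The case against.** The strongest reply is that SAP 7.3 is a list, not a model. It never says that baseline is an outcome row, and baseline adjustment fits at least as naturally with follow-up regressed on baseline, where clustering does enter the standard error. This stands, and it rules out saying that one particular fit was used. It does not rescue the text. That analysis is baseline-adjusted ANCOVA, so the difference-in-differences bullet would misdescribe it, and it still needs a small-sample correction that the SAP does not name.

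Second, a reader might infer that participants' repeated values are treated as independent. The protocol specifies repeated-measures mixed models and SAP 10 lists no departure from that, so omission of a participant effect is not shown. Adding one does not cure the problem, however: at ICC 0.039, CAC 0.8 and ρ 0.4 the stacked model rejects 18.2% with a participant intercept and 16.5% without (400 runs).

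Third, a reader might infer that baseline adjustment has no effect in the stacked model. That is wrong. It leaves the estimate alone only with complete data, and unless a participant intercept is also fitted it reduces the standard error. With follow-up missing in a way that depends on arm and baseline, the estimates with and without the covariate differ.

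Fourth, SAP 6 calls the secondary results exploratory. That limits the consequences, but the label is attached to the lack of multiplicity adjustment and does not make an interval valid.

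**Conclusion.** The point holds as a defect of specification that can produce wrong intervals on either reading. Under the stacked reading the effect's standard error omits mosque-by-time variation, and rejection is about 19% to 45% at the assumed values stated. With no such variation the interval is too wide (SE/SD 1.06 with the baseline covariate, 1.56 without it, at ρ 0.6). Under the follow-up-on-baseline reading, rejection is about 8% to 11% with a normal reference.

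Two stronger conclusions are tempting. One is that every continuous secondary interval is too narrow. The documents do not support it: they do not write the model, and they do not give the mosque-by-time variance that fixes both the direction and the size of the error. The other is that all secondary outcomes are affected. Binary outcomes have a separate specification ("Generalized estimating equations (GEE) were used for binary outcomes with robust SEs and exchangeable correlation structure"), whose robust standard errors capture mosque clustering if mosque is the grouping unit. SAP 7.3 does not state that unit, but the calculations here do not bear on it. The primary outcome is also untouched.

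Confidence is high that the text is incoherent and moderate as to the size of the effect.

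**What to change.** State one estimator in SAP 7.3, with its equation, and delete the other.

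- **Preferred.** Use the 4- and 12-month values as outcomes and baseline as a covariate. Fit arm, visit and arm-by-visit, with random effects for participant, mosque and mosque-by-visit, and Kenward-Roger or Satterthwaite degrees of freedom. Delete the difference-in-differences bullet.
- **Alternative.** Keep difference-in-differences on the 0-, 4- and 12-month values and remove the baseline covariate. Use the same three random effects and small-sample degrees of freedom.
- **Simple form of the alternative.** Compare mosque mean changes, 4 versus 4, on t with 6 df. This has a similar aim but is not equivalent to the mixed model: with three visits and balance, a mosque-by-visit effect is tested on (8 − 2) × (3 − 1) = 12 df, critical value 2.18, against 2.45 on 6 df.

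If results have already been produced under the present wording, state which model was fitted and rerun the continuous outcomes under the chosen one.

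The cost is a few lines of SAP text and model code, with no new data. Intervals will usually be wider, and with only eight mosques the mosque-level variance components will be imprecisely estimated.
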